#### Aggregation of the 20 N-of-1 trials

Data from all participants will be synthesized visually by Brinley Plots [29]. The clinical characteristics of responders and non-responders to the Unity system will be compared by non-parametric methods (Fisher's exact test and Wilcoxon's test). An estimate of the effect on the amputee population will be generated by aggregating each individual clinical trial (N-of-1 trial). Hierarchical Bayesian methods based on normal likelihood distributions [30] or non-normal likehood distributions [31] will be used. We will associate a non-informative prior distribution (Jeffreys' prior). By combining prior distributions and likelihood distributions, these methods provide probabilistic estimates of individual and group effects. Thus, the results of all completed phases will be combined to produce a posterior probability of the overall difference between Unity connected phases and Unity disconnected phases. The Unity system will be judged to be effective on the whole population if the highest density interval at 95% (HDI 95%) of the posterior probability of the mean difference favouring the treatment exceeds 0.975. It will be considered ineffective if the posterior probability of the average difference in favour of the treatment is below 0.025.

Data analysis will be conducted by a statistician blinded to phase allocation, using ABAB randomization tests with the ExPRT macro package (*Excel*^®^
*Package of Randomization Tests*) Statistical Analyses of Single-Case Intervention Data (Version 3.2, October 2018) developed by B.S. Gafurov and J.R. Levin [23], R (version 3.6) for Bayesian statistics and NAP calculator (https://jepusto.shinyapps.io/SCD-effect-sizes/).

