**Disadvantages to use a multiple N-of-1 trial methodology**
• Only treatments with true on/off effects can be explored and the condition must be stable. Therefore, any prosthetic/orthotic inducing cerebral plasticity (e.g.: thumb opponent splints in children) or requiring a long time for the patient to adapt/learn cannot be explored. This limits the range of prosthetic interventions that can be explored by multiple N-of-1 trials. • The population is smaller and may not be representative of the general population^a^. • Inability to explore statistically predictive factors^b^. • Inability to detect low-prevalence side effects.

^a^However, this problem is not specific to N-of-1 trials. Randomized controlled trials (RCT) claim in theory to provide a generalizable population outcome but they mask variability in response to treatment. Even in the most successful RCT study there are individuals whose behavior is not affected or is worsened by treatment, but these results are drowned out by a group mean.

^b^This is also true for randomized controlled trials (RCT). Power is calculated to demonstrate the effect of a treatment and not to determine predictive factors and responder characteristics.

The aim of the study is to evaluate the effectiveness of the Unity VASS on patient-reported comfort (using the Socket Comfort Score) during daily activities, in ecological environment, in patients with unilateral transtibial amputation blinded to the connection or disconnection of the Unity system, using a randomized, double-blind, multicenter prospective multiple N-of-1 trial. The secondary objectives are to evaluate whether Unity system leads to: (1) increased wearing time with the prosthesis, (2) increased number of steps per day, (3) decreased feeling of stump volume variation; (4) improved perception of limb-prosthesis fitting; (5) increased functional walking parameters.

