### Sample size calculation

#### Power calculation for each N-of-1 trial (i.e. each patient)

One method for calculating power in a single N-of-1 trial (i.e. for a single patient) is calculating the number of possible randomization assignments [25, 26] which depends on the type of randomization, the number of phases and the number of measurements per phase. The greater the number of possible assignments, the greater the possibility of detecting a treatment effect that exceeds the threshold of significance of 0.05 if an effect exists. With 4 true phase transitions, with a minimum duration phase of 7 days, a maximum study duration of 50 days, and 1 measurement per day, the number of assignments generated by this design is therefore 2300, allowing a significance of up to *p =* 0.0004 for each patient, as calculated on R package for single-cases [17].

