#### Number of subjects for the aggregation of the N-of-1 trials

For aggregating the multiple N-of-1 trials, we used the average comfort of a lower limb amputee 7.2/10 (SD= 2.3, inter-patient variance of 5.3) found by Hafner Brian et al. [19] and, (because of lack of data on Unity) our clinical experience that the Unity system would increase comfort by 2/10 points. Based on the calculation proposed by Senn [27] (formula 3 and 4 in the study) to calculate the necessary number of subjects and wanting to detect a clinical difference of 2, with an alpha at 5% and a power at 80%, and assuming that the intra-patient variance is 2, 16.35 subjects are required. If patients stop the study, they can contribute to the analysis of each completed phase. Recruiting 20 patients will allow to satisfy the sample size even in case of early dropouts.

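### Comparing responders with non-responders reduces each patient's measured Unity effect to yes/no, and with 20 patients this one exploratory comparison loses a substantial, assumption-dependent part of its power

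*Protocol article*

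**What the plan says.** Under Aggregation of the 20 N-of-1 trials, the protocol article states that "The clinical characteristics of responders and non-responders to the Unity system will be compared by non-parametric methods" and names the methods as "Fisher's exact test and Wilcoxon's test". It describes no other analysis that links a patient characteristic to the response.

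The same section plans Brinley plots and a hierarchical Bayesian model that yields an effect estimate for each patient as well as for the group. The section on each patient's N-of-1 trial adds NAP as an effect size for the daily outcomes.

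Table 1 lists "Inability to explore statistically predictive factors" among the disadvantages of the design. Its footnote adds that power is calculated for the treatment effect, not for responder characteristics. The aim and the five secondary objectives at the end of the Background do not include predictors of response.

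**The concern.** Each patient rates comfort daily for 50 days so that a connected-minus-disconnected difference can be estimated for that patient. In the comparison of characteristics, a patient just on the responder side counts the same as one with a very large gain. On the other side, Table 1 separates non-responders from patients who get worse, whereas this comparison names only two groups.

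Differential response is one of the reasons the Background gives for choosing this design, so readers will look at this comparison. If it has far less power than the same data could give, it will more often find that no characteristic separates responders from non-responders, and that finding may be over-read. The primary analysis, the individual randomization tests and the group estimate are not affected.

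**Working it through.** **The plan's own figures.** The article states no power for this comparison. The two figures it does give can be reproduced.

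- Group sample size: "assuming that the intra-patient variance is 2, 16.35 subjects are required". Take a patient-level difference with variance 5.3 + 2·2/2 = 7.3 (two AB cycles), a target difference of 2, two-sided 5% and 80% power. The normal approximation gives (1.960 + 0.842)² × 7.3 / 2² = 14.32. The noncentral t solution is n = 16.35, as stated.
- Assignments per patient: C(50 − 4·7 + 3, 3) = C(25, 3) = 2300, and 1/2300 = 0.0004, as stated.

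So 20 patients are sized for the mean effect. Nothing is sized for the comparison of characteristics.

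**Information kept by a split.** For a normally distributed effect cut so that a share p are responders, the asymptotic efficiency relative to the uncut effect is φ(c)² / [p(1 − p)], where c is the cut in SD units. This gives 64% at p = 0.5, 58% at p = 0.7 and 49% at p = 0.8.

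**Power at n = 20.** Inputs from the article: 20 patients and the two named tests. Assumptions, because the article gives no values: normal effects; responder share 50, 70 or 80%; correlation 0.3 or 0.5 for a continuous characteristic such as age; a difference of 1.05 or 1.32 within-group SD for a binary characteristic held by 10 of 20 patients. A shift of 1.05 SD corresponds to responder rates of 30% v 70% (2 × 0.524). Tests are two-sided at 5%, with 8000 simulated data sets per setting (Monte Carlo standard error at most 0.6 percentage points).

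| Characteristic | Test on the measured effect | After the split: 50 / 70 / 80% responders | Share of power lost |
|---|---|---|---|
| Continuous, r = 0.3 | Spearman 22% | Wilcoxon 16 / 14 / 11% | 27 / 36 / 50% |
| Continuous, r = 0.5 | Spearman 57% | Wilcoxon 40 / 35 / 29% | 30 / 39 / 49% |
| Binary, 1.05 SD | Rank-sum 55% | Fisher 25 / 20 / 11% | 55 / 64 / 80% |
| Binary, 1.32 SD | Rank-sum 75% | Fisher 40 / 32 / 17% | 47 / 57 / 77% |

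The share lost is (power on effect − power after split) / power on effect; for example (57 − 40)/57 = 30%.

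With no association, Fisher's test rejects in about 1% of data sets and the rank-sum test on the effects in 4 to 5%. Fisher's conservatism therefore adds to the loss from the split. Ranking is not the cause: at r = 0.5 Pearson reaches 64%, and at 1.32 SD the t-test reaches about 80%, both close to the rank tests on the measured effect.

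**A case that can be checked by hand.** Suppose 16 patients respond and 4 do not, and the characteristic divides the patients 10 v 10. The most extreme table puts all 4 non-responders on one side. Its two-sided Fisher p-value is 2 × C(10,4)/C(20,4) = 2 × 210/4845 = 0.087. In that configuration Fisher's test can never reach 5%, however strong the association.

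**Wider range.** Over correlations of 0.3 to 0.7 and differences of 0.8 to 2.0 SD, with the same responder shares, the loss relative to the parametric test on the measured effect runs from 19% to 84%. It is material throughout, but no single figure is fixed.

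**The case against.** The strongest reply is that the article has already disclosed the limit. Table 1 says predictors cannot be explored statistically, its footnote says power was not calculated for them, and the comparison is one sentence outside the objectives. Fisher's and Wilcoxon's tests are valid for the comparison described. Most of this stands, and it is why the point is minor. But the disclosure concerns the sample size; it gives no reason to discard further information from the same 20 patients when their individual estimates will be available.

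A second reply also stands: the alternative does not rescue the analysis. At r = 0.3 Spearman has only about 22% power, and at r = 0.5 about 57%. As a yardstick, with the variance of 7.3 that reproduces the plan's sample size, 1.05 SD is 1.05 × √7.3 = 2.8 comfort points, so even the settings with better power assume large differences.

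Three stronger readings are tempting and not supported:

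- A reader might infer that the split costs about half the power. That lies within the range, but the documents give neither the responder share nor the strength of association.
- A reader might infer that the plan as a whole throws away the size of each patient's effect. It does not: NAP, the Brinley plots and the Bayesian individual estimates keep it. Only this comparison drops it.
- A reader might argue that the answer shifts with the responder cut-off. The article states no numerical cut-off. One may stand in the full protocol or the analysis plan, so its absence is not counted here.

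**Conclusion.** The point holds as a limited criticism of one analysis choice. Testing characteristics against responder status wastes information that the trial will have, and the loss at 20 patients is substantial: roughly 30 to 50% of the power for a continuous characteristic at r = 0.5, and roughly 45 to 80% for a binary one at 1.05 to 1.32 SD. These figures rest on normal effects, 50 to 80% responders and, for the binary case, an even 10 v 10 division. They take the association with the estimated effect as given, so estimation error within patients is already absorbed in r and in the SD. No result the plan relies on for its main conclusions changes. This is an improvement at no cost in data, not a flaw that endangers the trial.

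**What to change.** Replace the two-group test by an analysis of the individual effect estimates that the plan already produces:

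- a rank-sum test of the effects across the levels of a categorical characteristic, such as activity level or cause of amputation;
- Spearman's correlation for age and other continuous characteristics;
- or, alternatively, the characteristic as a patient-level covariate on the treatment effect in the planned hierarchical model. This also carries the uncertainty of each patient's estimate; its power was not simulated here.

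Label the analysis exploratory, in line with Table 1. State that it remains underpowered for moderate associations, so that a null result says little. Keep the table of responders and non-responders as description, without tests.

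The cost is a change of wording in the analysis section and a few lines of code. No visits, data or patients are added, and the primary analysis is untouched.

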## Discussion

This study brings innovative elements in assessing ecological comfort and using multiple N-of-1 trial methodology in the prosthetic field. Previous research suggested that VASS improved slightly gait parameters, but none assessed comfort as the main outcome, and not ecologically as we intend to. Further, most research focuses on limiting prosthetic-related problems (e.g.: sores, volume loss), or walking parameters, while the main patient’s priority, after these are sufficiently addressed, is comfort. To adequately use multiple N-of-1 trials, a true on/off effect is needed, which connecting/disconnecting Unity allows perfectly. Double-blinded randomized trials are rarely feasible in the prosthetic field, which is another strength in this project. Finally, having a single prosthetist to manufacture all the devices in a given center, should reduce inter-patient variability due to technical issues, and concentrate the N-of-1 trial on inter-individual differences due to the Unity system being tested.

Multiple N-of-1 trials represent a switch in the rationale behind the choice of a medical device: instead of selecting prosthetics based on the mean response to the device, multiple N-of-1 trial allows to answer the question “which device is best for THIS patient”, using a rigorous, recognized scientific methodology. Moreover, it allows to obtain individual results, as well as group results, with greater power than usual RCTs (often including insufficient samples of amputees). Using PROMs (and especially comfort) and ecological repeated measures, the results obtained by this trial are more likely to correspond to the true effectiveness of the prosthesis in daily life and in patients’ personal activities. Double blind multiple N-of-1 trials could be the methodology that adds objectivity to patient’s usually subjective choice of a prosthesis, increasing therefore science contribution above marketing contribution in this highly competitive field. Extending this rationale to decisions of funding of expensive devices, a future health policy could be to fund a costly device only for patients showing a statistically significant improvements based on a N-of-1 trial, rather than using general funding criteria. Using PROMs can be a strength as they give insight into patient’s subjective appreciation of the prosthesis, but PROMs may be very biased if they relate to costly devices without blinding to the condition. Here, we hope that blinding will allow PROMs to be less biased. Thus, showing objectively a benefit could allow many people with transtibial amputation to upgrade their comfort in their daily life.

Some limitations must be highlighted. Firstly, the funder of this study is the Össur company, which has created and sells the Unity system. However, the company does not participate in the interpretation of data or in drafting this manuscript. A result report will be prepared for the High Authority of Health (organization that decides the types of prosthetics funded by the health system in clinical care in France) but publishing the protocol prior to the trial will ensure that the methodology is not changed or results not interpreted in a biased way. Secondly the order of phases in N-of-1 trials should be completely random, while here all patients begin the study with a Unity disconnected phase (after an acclimation time with the Unity connected). This was decided because a ceiling effect (high SCS) was expected even without Unity connection i.e. before knowing that a better comfort is possible, patients are likely to rate SCS as very high, (as long as they have no sores or obvious discomfort). This phase order was expected to educate the patients to be aware of their comfort, but is criticizable, as it may induce lower rating of SCS after Unity’s first disconnection. Finally, usual randomization in N-of-1 trial are block randomizations with equal phases length. Phase length randomization (giving unequal phase lengths) comes from behavioral research and is less used in medicine. Here the latter was preferred, in order to obtain a statistical significance and a power calculation for each N-of-1 trial separately.

## Data Availability

The datasets generated and/or analysed during the current study are not publicly available due to third party (Össur France) restrictions but might be available from the corresponding author on reasonable request.

## Abbreviations

PROMs: Patients-Reported Outcomes Measures;
RCT: Randomized Controlled Trial;
SCS: Socket Comfort Score (or Socket Prosthetic Comfort Score);
VASS: Vacuum-Assisted Suspension System
